### Sample size calculations

This is an exploratory study where the initial sample size for recruitment is set to 200 women in the COVID-19 group and 1000 in the screening group (with an additional 10%–15% with assumed positive tests in the screening group thus more than 300 COVID-19 cases). Sample size has been calculated with 80% power and a significance level of <0.05 based on the assumptions shown in table 3. As outcomes are retrieved from population-based registers, there will be close to complete follow-up.

**Table 3 T3:** Assumptions for power calculation

Outcome	Prevalence in screening group	Prevalence in COVID-19 group	Sample size screening group	Sample size COVID-19 group
Pre-eclampsia	6%	12%	511	256
Thrombosis	0.13%	2%	613	306
Small for gestational age (below 10th percentile)	10%	20%	199	199
Preterm delivery	6%	12%	511	256
Neurological and/or neurodevelopmental disorders	1%	4%	581	290

The percentage of women with vertical transmission secondary to active COVID-19 at the time of delivery (14 days before to 2 days after delivery) will be calculated.

Depending on the prevalence of malformations, the presence and type of malformations in case of infection during early pregnancy will be presented in a purely descriptive manner.

The presence of antibodies in umbilical cord blood and breast milk will be studied in relation to gestational week of infection, severity of infection and maternal serum antibody levels. Antibody levels will be followed over time.

Due to the unprecedented nature of the pandemic, it is difficult to perform formal power calculation with regard to parent health and mental well-being.

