**COVID-19 group—mothers**	
Antenatal screening	Pre-existing samples taken as part of routine antenatal care and screening. More details under ‘biological samples from women and newborns’.
On being diagnosed with SARS-CoV-2 infection	Nasopharyngeal and pharyngeal swabs or saliva
	Blood 30 mL
	Vaginal swab
	Rectal swab
	Urine 10 mL
At delivery or in case of pregnancy loss/termination of pregnancy	Nasopharyngeal and pharyngeal swabs or saliva
	Blood 30 mL
	Placenta, 12 pieces, in total approximately 10–15 cm^3^
	Vaginal swab
	Rectal swab
	Urine 10 mL
	Placenta/membrane swab (in case of COVID-19 within 14 days before delivery or COVID-19 diagnosis up to 2 days after delivery)
In case of Caesarean section	Amniotic fluid 10 mL
In case of spinal anaesthesia, e.g. at caesarean section	Cerebrospinal fluid 5 mL
At 48–96 hours follow-up post partum	Breast milk 5–10 mL
Follow-up within 12 months post partum	Blood 10 mL
	Breast milk 5–10 mL

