**COVID-19 group—children**	
At birth	Umbilical cord blood 7 mL In case of stillbirth: Nasopharyngeal and pharyngeal swabs or saliva and blood 5 mL from heart puncture. These samples are routinely performed as standardised clinical practices in case of stillbirth.
Within 12 hours of delivery	Nasopharyngeal and pharyngeal swabs (in case of maternal COVID-19 within 14 days before delivery or COVID-19 diagnosis up to 2 days after delivery)
48–96 hours post partum	Nasopharyngeal and pharyngeal swabs
	Rectal swab
	Blood 5 mL (in case of maternal COVID-19 within 14 days before delivery or COVID-19 diagnosis up to 2 days after delivery)
Follow-up within 12 months post partum	Blood 5 mL

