### Exposure definition in regard to clinical outcomes

Based on RT-PCR and serology and data from SmiNet, women will be divided into infected women (COVID-19 during pregnancy) and non-infected women (no COVID-19 during pregnancy). In some analyses/subanalyses, gestational age at infection, severity of disease, viral load and immune response will be considered as additional exposure variables for the infected group.

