### Examples of outcome definition

Pregnancy and neonatal outcomes will be retrieved from the SPR and SNQ, either registered as tick boxes, actual measures or International Classification of Diseases 10th revision (ICD-10) codes: Pre-eclampsia (ICD-10 O14), gestational age at birth, preterm delivery (with subanalyses for early, moderate, late preterm delivery as well as spontaneous vs iatrogenic preterm delivery), birth weight, small for gestational age, birth asphyxia, and perinatal death.Thromboembolic event diagnosis will be retrieved from the SPR and the National Patient Register (ICD-10 I82, I26).Vertical transmission as defined by Shah *et al.*
38
Child development and health: Developmental delays or potential delays as measured by ASQ up to 4 years of age. Neurological disorders diagnosed during the first 4 years of life (composite) retrieved from the National Patient Register; Any mental or behavioural disorder (ICD-10 F00–F99), impaired vision (H54), impaired hearing (H90, H91), cerebral palsy and other paralytic syndromes (G80–G83).Presence of antibodies in umbilical cord blood (IgG, IgM) and breast milk (IgG, IgM, IgA).

Subanalyses will be performed to study the impact of country of birth, socioeconomic status or underlying disease in the mother (eg, obesity, hypertension, diabetes, asthma).

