### General statistical methodology

Demographics will be presented as numbers (percentage), medians or means as appropriate by distribution. Comparisons between groups will be analysed by Student’s t-test or Mann-Whitney U-test with means or medians and confidence intervals or IQR, as appropriate according to distribution of the variables. Categorical variables will be compared by χ^2^ test or Fisher’s exact test. Correlations will be analysed by Pearson’s r or Spearman’s r as appropriate by distribution of the variable. Regression analyses, unadjusted and adjusted, will be performed to adjust for known confounding variables. Ten cases per variable at the lowest will be considered appropriate to avoid overfitting of the model.

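### Cord-blood IgG is planned as a yes/no outcome although levels are measured; if most infants are positive, this costs much of the power to detect a relation with week, severity or maternal level

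*Protocol article*

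**What the plan says.** The outcome scale appears in two places in the protocol article. Under Examples of outcome definition the entry reads "Presence of antibodies in umbilical cord blood (IgG, IgM) and breast milk (IgG, IgM, IgA". Under Sample size calculations, "The presence of antibodies in umbilical cord blood and breast milk will be studied in relation to gestational week of infection"; the same sentence adds severity of infection and maternal serum antibody levels as the other factors. Maternal serum therefore enters as a level, while cord blood and milk enter as presence.

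The next sentence is "Antibody levels will be followed over time". It names no compartment. In Table 1 the COVID-19 group gives cord blood once, at birth ("Umbilical cord blood 7 mL"). Milk is taken at 48–96 hours and again at the visit listed as "Follow-up within 12 months post partum".

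Two other places bear on this. Exposure definition says that in some analyses "gestational age at infection, severity of disease, viral load and immune response will be considered as additional exposure variables for the infected group". General statistical methodology says "Correlations will be analysed by Pearson’s r or Spearman’s r as appropriate by distribution of the variable", and also names the Mann-Whitney test. Neither is tied to cord-blood or milk levels. The article gives no positivity rate, assay cutoff or distribution, and Table 3 has no antibody outcome.

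**The concern.** The question is how antibody in the infant varies with the timing of infection, its severity and the mother's own level. For cord IgG, presence may be close to universal among infants of seropositive mothers. If so, the outcome hardly varies: an infant just above the cutoff and an infant with a very high level count the same. A null result could then come from the scale and not from equal transfer.

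The sentence on following levels over time does not settle this for cord blood. A single sample at birth cannot be followed over time, and the sentence does not relate level to week, severity or maternal level.

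**Working it through.** **Inputs from the protocol article.** 200 women recruited to the COVID-19 group, and more than 300 infected women once positives from the screening group are added; 80% power and 5% significance; at least ten cases per variable in regression; three named factors (week, severity, maternal level).

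**Assumptions, not in the documents.** Log level is normal; its correlation with the factor of interest is r = 0.20; the share positive, p, is varied.

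**The plan's own figures.** None exists for antibodies. Table 3 reproduces to within one woman with a two-sided 5% test, pooled variance and no continuity correction (512/256, 613/307, 199/199, 512/256, 581/291). The two-sided 5% convention is therefore used below.

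**Step 1: simple upper bound on the loss.** If the level were fully observed, the information kept by a cut with share p positive is φ(z_p)² / [p(1−p)]. At p = 0.90: z = 1.2816, φ = 0.1755, and 0.0308/0.09 = 0.342, so 66% is lost. The loss is 36% at p = 0.50, 51% at 0.80, 78% at 0.95 and 88% at 0.98.

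**Step 2: approximate power on presence.** Multiply r by the square root of the share kept and use Fisher's z: power = Φ[atanh(r′)·√(n−3) − 1.96]. With n = 200 and r = 0.20, the fully observed level has 81%. At p = 0.90, r′ = 0.20 × √0.342 = 0.117, and Φ(1.65 − 1.96) = 38%. The other values are 62% (p = 0.50), 51% (0.80), 27% (0.95) and 16% (0.98).

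**Step 3: a fair comparator.** A real assay does not return a value below its cutoff, so step 1 compares with an analysis that cannot be done. The fair comparison sets all values below the cutoff to one tied value and uses Spearman's correlation. Simulated power, n = 200, r = 0.20:

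| Share positive | Presence | Left-censored level |
|---|---|---|
| 10% | 37% | 37% |
| 20% | 51% | 52% |
| 30% | 58% | 60% |
| 50% | 62% | 70% |
| 80% | 51% | 77% |
| 90% | 38% | 78% |
| 95% | 25% | 77% |

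A separate run of 20,000 simulated studies agreed with every entry to within about 1.5 percentage points.

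Turned back into information, the share kept is [(1.96 + z_presence)/(1.96 + z_level)]², where z is the normal quantile of the power. At 50% positive: (2.265/2.484)² = 0.83, a loss of about 17% and not 36%. At 90%: (1.655/2.732)² = 0.37, a loss of about 63%.

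**Step 4: number of negatives.** Among 200 women there are 40 negatives at 80% positive, 20 at 90% and 10 at 95%; among 300 there are 60, 30 and 15. If the ten-cases rule is applied to the smaller category, as is usual for a binary outcome, three one-term factors need 30 negatives. That holds up to 85% positive with 200 women (30/200 = 15%) and up to 90% with 300 (30/300 = 10%).

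**The case against.** **The size is conditional.** A reader might infer that presence discards 36% to 88% of the information and leaves almost no contrast. The documents do not support that as a fact. The range needs 50% to 98% positivity and a fully observed normal level. Against the censored level the loss at 50% positive is about 17%, and at 30% or below the gain from using level all but vanishes. Even at 80% positive, 40 of 200 infants would be negative.

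**One argument does not fit every antibody.** The list covers IgG and IgM in cord blood, and IgG, IgM and IgA in milk. High positivity is plausible chiefly for cord IgG. Women infected shortly before delivery are included, which could lower it even there. Nothing in the documents suggests high positivity in milk.

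**Levels are not excluded.** A reader might also infer that the plan ignores levels altogether. It does not: levels are to be followed over time, and that sentence can cover maternal serum and the repeated milk samples. Rank methods are already named. No cutoff or binary model is written down, and the study may hold the raw values for later use.

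**An article condenses.** The outcomes are headed as examples, details of the research questions go to a supplement that is not shown, and the study is called exploratory. Handling of values below a detection limit could properly sit in an analysis plan, and its absence here is no fault.

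All four points stand as limits on size and weight. They do not remove the point for cord IgG: the article twice names presence as the outcome and sets it against a maternal level. That is a stated scale, not a detail left out.

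**Conclusion.** The point holds for cord-blood IgG and is conditional on positivity. If 80% to 95% of infants are positive, presence has 25% to 51% power where the left-censored level has 77% to 78%. At 50% positive the gap is 8 points (62% against 70%), and at 30% or below it is negligible. These figures rest on n = 200, r = 0.20 and a normal log level, all but the first assumed. For milk the case is weaker, because positivity may be low and the sentence on levels may already apply. For cord IgM the point does not apply if few infants are positive.

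No stated figure is wrong, and no sample size depends on this outcome. It is a worthwhile, inexpensive improvement to an exploratory analysis.

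**What to change.** In Examples of outcome definition and in the antibody paragraph of Sample size calculations:

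- Make log cord-blood IgG level the outcome analysed against gestational week of infection, severity and maternal serum level.
- Treat values below the assay cutoff as left-censored (for example a Tobit model), or use the rank methods already named in General statistical methodology.
- Report presence of cord IgG as a descriptive percentage.
- Do the same for milk antibodies where the assay gives a quantitative result.
- Keep presence as the outcome for cord IgM.

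The cost is a change of wording. The same samples serve, provided the cord-blood assay is quantitative. The practical demands are a rule for values below the limit and one assay scale for all samples compared.

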## Patient and public involvement

A pregnant patient representative, her partner and a patient organisation namely, the Swedish Association for Premature Infants (Svenska prematurförbundet) were invited to participate in the early stages of planning the study. Several video meetings were held between a research group representative (KL) and the patient representative and her partner where the research questions and outcomes were discussed. Participant time investment in the study was discussed and adjustments in the questionnaires were made according to their feedback. The opinion and feedback obtained from the non-pregnant parent were also given special importance.

The study website (www.copestudien.se) was designed in collaboration with the patient representative and provides a convenient platform for participants to connect with the research team. Communication with the wider pregnant population and the public through social and mass media has enabled uptake of patient-evoked research questions and led to appropriate modifications in the study protocol.

## Ethics and dissemination

COPE is a comprehensive cohort study involving the use of register based data, biological sampling, questionnaires and interviews. The study has received national ethical approval by the Ethics Review Board, Lund, Sweden (dnr 2020-02189 and amendments 2020-02848, 2020-05016, 2020-06696 and 2021-00870) and national biobank approval at Biobank Väst (dnr B2000526:970). Confidentiality aspects such as data encryption and storage comply with the general data protection regulation. All data are stored in a secure online database provided by MedSciNet (www.medscinet.com), an international company specialising in web applications in the field of academic medicine. Biobank samples will be identified using the personal identification numbers of the patients included in the study and pseudonymised after identification in the biobank before laboratory analyses.

Several blood and tissue samples are being collected in the study. Certain samples are collected as part of the standardised diagnostic protocols of the COVID-19 pandemic (eg, nasopharyngeal swabs) while others are study specific (eg, blood samples from infants up to the age of 12 months). Sampling will be performed by experienced nurses and the application of a topical anaesthetic patch will help minimise pain for the child.

Results from this study will be presented at different national and international conferences, in peer-reviewed journals and in mass media. Wide-spread public interest in COVID-19-related research will help facilitate study dissemination and participation from all major Swedish maternity units.

## Discussion

Knowledge from previous coronavirus outbreaks^1 4^ has identified pregnant women as particularly susceptible to negative outcomes. While evidence is increasing on how SARS-CoV-2 infection in pregnancy can affect pregnancy outcomes,^9^ there is a need to thoroughly examine the burden of COVID-19 during the pregnancy with focus not only on the pregnant woman and the fetus but also the child after delivery and the pregnant woman’s partner. In addition, long-term consequences of COVID-19 during pregnancy are also relatively unknown.

Local and regional differences in the testing and management of pregnant women with SARS-CoV-2, make the results of published studies difficult to interpret. Many studies do not report the gestational age at infection, do not include a control group, recruit women only when they seek healthcare for obstetric complications or on admission for delivery, do not specify the indication for an obstetric intervention (intervention with or due to COVID-19) or are not generalisable since they are based on a single site with a population having a certain risk profile regarding, for example, socioeconomic status or pregnancy complications.^4^ It can, therefore, be argued that current guidelines on how to monitor and treat pregnant women and their neonates are based on inadequate evidence with little or no data on long-term follow-up.

Few studies have focused on women’s experience of pregnancy, childbirth and early parenthood during the COVID-19 pandemic and the results are often context specific, making them difficult to generalise. Partner experience has been largely overlooked^22^ and there is a lack of data on pregnancy and child outcomes secondary to SARS-CoV-2 infection in early pregnancy. Viral infections have been known to cause developmental problems for the fetus such as deafness (cytomegalovirus)^39^ or anaemia (parvovirus).^40^ Due to the novelty of SARS-CoV-2, the effect of the virus on fetuses in the first trimester is largely unknown.

However, the study design has certain limitations. Although the majority of all maternity units are participating, the study will not be completely representative of the total population. Since women and partners need to actively consent to participate, there will be self-selection bias. Additionally, the questionnaire and interview parts of the study require adequate language skills as described earlier. During the 4-year follow-up period, a certain degree of ‘drop-out’ is expected in the questionnaire part of the study. With regard to the biobank part of the study, we expect maternity units to show considerable variation in retrieving a full list of samples as the healthcare sector is under enormous pressure due to the pandemic.

To summarise, the COPE study will help lay the foundations for understanding the society’s ability to protect one of its most vulnerable groups, pregnant women and their children.^22^ The COPE database and biobank will help answer important questions regarding short and long-term complications secondary to COVID-19 in pregnancy and can be used for future research on the prevention of other pregnancy complications after viral infections. The collaboration and research infrastructure built within the COPE study has the potential to facilitate future research within obstetrics and neonatology in Sweden.
